## 8.5 DATA MANAGEMENT

The data management plan describes the trial-specific approach of the individual processes for traceability and completeness of the relevant data.

The persons responsible for data management are responsible for data administration and processing. This is done by using an electronic data capture software for clinical trials that meets the requirements of the applicable laws and guidelines (especially GCP). The scope of database access and the associated authorizations are regulated by appropriate user roles.

The data is checked for completeness, plausibility and consistency by means of programmed checks directly in the eCRF and by additional manual checks outside the eCRF. Any queries arising in the process are sent to the respective trial site directly in the eCRF. Queries as well as responses or corrections are made directly in the eCRF. Changes to the data are reproduced in the audit trail.

The data is backed up on a daily basis. The data storage facilities are located in a locked room of the Medical Faculty of the TU Dresden, to which only the responsible system administrators have access.

At the end of the trial, the database is closed after all data relevant to the trial protocol has been entered and all queries have been clarified. Subsequent changes to the data can only be made with the consent of the principal coordinating investigator (PCI).

## 8.6 DATA STORAGE

### 8.6.1 STORAGE OBLIGATIONS OF THE TRIAL SITE

Records and documents related to the trial or distribution of IMPs (e.g., data collection forms, informed consent forms, drug accountability log, and other relevant documents) must be retained at the trial site in accordance with the regulatory requirement, but for at least 25 years.

Subject records and other original data must be kept for the longest possible period of time permitted by the hospital, institution or private practice, but at least 25 years.

### 8.6.2 STORAGE OBLIGATIONS OF THE SPONSOR

The sponsor is responsible for creating and maintaining a central trial master file (TMF) in accordance with ICH-GCP and for keeping it access-protected during the trial. It contains all

essential documents of the clinical trial. After termination or discontinuation of the trial, the TMF must be retained by the sponsor in accordance with the legal requirements, but at least for a period of 25 years.

## 9 MONITORING AND AUDIT

### 9.1 ACCESS TO SOURCE DATA

The investigator must allow all authorized third parties access to the trial site and to the subject's records (including direct access to source data and texts) in accordance with applicable legal requirements. Authorized third parties include monitors, auditors, and other persons authorized by the sponsor as well as the Member States concerned. All these persons are bound to secrecy.

### 9.2 MONITORING

The continuous monitoring of a clinical trial is an indispensable instrument of quality assurance and is risk-based according to ICH-GCP.

The monitoring includes initiation and monitoring visits for source data verification as well as final visits for the proper closure of the trial site. During the conduct of the trial, remote and central monitoring procedures are combined with on-site visits to achieve high protocol compliance and data quality, and to ensure subject's safety and rights.

Detailed information on the scope, procedure and contents of the monitoring as well as procedures to ensure data quality and necessary measures in case of protocol deviations are described in the monitoring plan.

#### **Source data verification (SDV)**

In addition to providing access to all documents related to the trial, including the original trial-relevant subject records, the trial site must maintain the subject record as complete as possible, i.e., record information on medical history, concomitant diseases, trial enrolment, visit dates, trial results, IMP dispensation, and (serious) adverse events.

The monitor is also enabled to perform data review and comparison with the relevant subject records in accordance with the Standard-Operation-Procedures (SOPs) and ICH-GCP guidelines at pre-determined intervals to ensure compliance with the protocol and continuous data recording. All original medical records that are required as the source of the information in the eCRF are reviewed. The trial subject has agreed to such verification by signing the trial-specific informed consent form.

Monitoring tasks are e.g.:

- verifying that the trial site meets the requirements of the clinical trial according to the trial protocol (subject population, equipment, etc.) and GCP guidelines,
- initiation of the trial site,
- verification of informed consent forms,
- checking the ISF for completeness and actuality,
- source data verification,
- verification of proper reporting of SAEs,
- verification of compliance.

The monitor is obliged to treat all information confidentially and to uphold the fundamental right of the subjects to integrity and protection of their privacy.

### 9.3 AUDIT/INSPECTION

In order to guarantee that the trial is conducted in accordance with GCP guidelines, audits can be carried out on behalf of the sponsor. The auditor is independent of the persons involved in the trial.

During the audit, the following points are checked, among others:

- quality of the trial according to GCP guidelines,
- performance of the trial according to the trial protocol,
- validity of the data.

After each audit, the trial site receives an audit confirmation from the person responsible for the audit. This confirmation must be kept in the ISF so that it is available in case of an inspection by the Member States concerned. A corresponding audit report is also sent to the trial site and the Sponsor.

In addition, inspections can be carried out by the responsible Member State concerned in accordance with the Regulation (EU) No 536/2014. In case of an announcement of an inspection, the trial site must inform the sponsor immediately.

## 10 STATISTICS

A general description of the sample size calculation and the statistical methods to be used to analyze this study are outlined below. More details will be provided in the statistical analysis plan (SAP).

### 10.1 STATISTICAL HYPOTHESES

#### Study objective

The main goal of this study is to demonstrate that the TTV-guided immunosuppression (arm T) is non-inferior with respect to safety compared to standard dosing (arm S) in stable adult kidney transplant recipients with low immunological risk in the first year after transplantation.

#### Non-Inferiority hypothesis:

The primary objective is to demonstrate the non-inferiority of TTV-guided immunosuppression (arm T) compared to standard dosing (arm S) in stable adult kidney transplant recipients with low immunological risk in the first year after transplantation.

Non-inferiority can be concluded if the upper limit of a two-sided 95% CI for the difference in proportion of patients at month 9 after randomisation (= Visit 7; post-transplant month 12) between the two treatment arms is less than 10% points.

Let  $p_T$  and  $p_S$  be the proportion (in %) of participants in the arm T and arm S, respectively, then the primary statistical hypothesis can be formulated as follows:

$$H_0: p_T - p_S \geq 10 \% \text{ versus } H_1: p_T - p_S < 10 \%$$

#### Superiority hypothesis:

If non-inferiority is reached, the study will demonstrate superiority of TTV-guided immunosuppression (arm T) compared to standard dosing (arm S) in the same endpoint by testing the hypothesis:

$$H_0: p_T - p_S \geq 0 \text{ versus } H_1: p_T - p_S < 0$$

#### Null hypothesis

TTV-guided immunosuppression is not safe compared to standard dosing in stable adult kidney transplant recipients with low immunological risk in the first year after transplantation.

### 10.2 SAMPLE SIZE CALCULATION

For the sample size calculation, we analysed the occurrence of the primary endpoint (infection, allograft rejection, death and graft loss) in recipients of a kidney allograft transplanted between 1.1.2012 and 31.12.2018 at the Vienna centre, applying the trial-specific inclusion and exclusion criteria (unpublished data). Overall, 40% of patients experienced the primary endpoint between month 3 and 12 after transplantation. Therefore, we assume a composite rate of around 40% in the standard dosing (arm S).

It is expected that the TTV-guided immunosuppression (arm T) reduces the occurrence of the primary endpoint, and therefore rates between 20% and 30% are assumed to be reasonable.

The non-inferiority margin has been fixed 10% points (see also above). Thus when the sample size in each group is 120, a two-group large-sample normal approximation test of proportions with a one-sided 2.5% significance level will have 90.42% power to reject the null hypothesis

that arm T is inferior to standard arm S (the difference in proportions,  $\pi_1 - \pi_0$ , is 0.1 or farther from zero in the same direction) in favour of the alternative hypothesis arm T is not inferior to arm S, assuming that the expected proportions are 0.3 and 0.4 in arm T and S, respectively (i.e. assuming a better outcome in arm T).

Due to the planned observation period of 9 months and the special patient population, a rather low drop-out rate is expected of about 2-5%. Adjusting for potential drop-outs, the sample size is fixed with 130 patients per group, i.e., 260 in total.

The sample size calculation was performed using N-Query Version 8.6.1.

## 10.3 STATISTICAL ANALYSIS

### 10.3.1 DEFINITION OF EVALUTION POPULATIONS

The primary analysis will be performed on a modified intention to treat (mITT) principle. Sensitivity analyses will be performed according to intention to treat and per protocol (PP) analysis, and the dataset restricted to adherent patients. Further sensitivity analyses are described below.

Different analysis sets are defined as follow:

#### **mITT set**

This analysis set includes subjects who were randomized. According to the intent to treat principle, subjects will be analyzed according to the treatment they have been assigned to during the randomization procedure. The mITT includes all patients who are eligible for the study and with at least one TAC evaluation (and potential adaption) during visit 1 will be included in the analysis.

#### **PP set**

This analysis set comprises all subjects who received study intervention and did not critically or majorly violate the protocol in a way that might affect the evaluation of the effect on the primary objective. A list of potential protocol deviations is given in section 6.14.

#### **Adherent set**

Medical adherence will be defined by patient diary; see 5.10

### 10.3.2 BASELINE PARAMETERS AND CONCOMITANT MEDICATIONS

Baseline parameters, medical history and concomitant medication will be documented during screening and throughout the trial until the last follow-up visit. Enrolment, protocol deviations and discontinuations from the study drug and the study will be summarized. Demographics (e.g. age, race, ethnicity and sex) and medical history and concomitant medication will also be summarized by treatment group. For qualitative variables (e.g. sex), absolute ( $n=x$ ) and relative frequencies will be calculated per treatment group. Data will be visualized by bar plots. For quantitative data (e.g. age), the number of valid observations ( $n=x$ ), mean, standard deviation, standard error, median, minimum and maximum will be calculated for each treatment group and each time point separately. Data will be visualized by spaghetti plots (showing individual patient profiles over time), boxplots and histograms.

### 10.3.3 STATISTICAL ANALYSIS OF THE PRIMARY END POINT

The occurrence of the primary composite endpoint will be presented per treatment group as absolute numbers and percentages. The difference of the occurrence of the primary endpoint between the two treatment groups and a two-sided 95% confidence interval will be calculated.

Non-inferiority will be concluded if the upper limit of a two-sided 95% confidence interval for the difference in proportion of patients at month 9 after randomization (= Visit 7; post-transplant month 12) between the two treatment arms is less than 10% points. Superiority will be concluded if the confidence interval excludes 0.

As additional sensitivity analyses confidence intervals will be calculated being adjusted for study stratifications (such as centers) using Cochrane-Mantel-Haenszel weights. Also logistic regression models will be used using additional factors (such as sex) and covariate (such as age at randomization).

To explore the composite endpoint further, it will be also be analyzed as time-to-event endpoint considering the time from randomization till time of first event. We will visualize these data by presenting Kaplan-Meier curves for each treatment arm. Furthermore, Cox-regressions models will be performed adjusting for the same factors and covariates as used in the logistic regression models.

To address the repetitive nature of the events used in the definition of the primary endpoint, we will also perform supportive analyses for recurrent event data. We will fit a negative Binomial regression model for the events of the composite endpoints accounting for the time a patient is under risk. Furthermore, we will perform the counting process model of Andersen-Gill and frailty models.

To assess the impact of the individual components of the composite endpoints, each component will be analyzed descriptively (see description for secondary endpoints).

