| Investigational Medicinal Product | 
Active substance: TAC
 
Trade name: All products containing TAC and authorized in participating countries
 
Manufacturer: All manufactures of authorized products
                                                                                                                                                                                                                                                                                                                                                                                                                                                                                                                                                                                                                                                                                                                                                                                        |
| Treatment Schedule                | 
Active group
 
Product: TAC
 
Dose: Dependent on TTV level (target 4.6 to 6.2 log10 c/mL) quantified by real-time PCR kit TTV R-GENE® in the plasma
 
Duration: 9 months
 
Control group
 
Product: TAC
 
Dose: According to local centre standard
 
Duration: 9 months
                                                                                                                                                                                                                                                                                                                                                                                                                                                                                                                                                                                                                                                     |

|                          |                                                                                                                          |
|--------------------------|--------------------------------------------------------------------------------------------------------------------------|
| Including Centres | Berlin, Dresden, Graz, Grenoble, Groningen, Innsbruck, Leiden, Linz, Prague, Regensburg, Strasbourg, Valencia and Vienna |

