### 5.7.6 CONTROL GROUP

**TAC will be dosed according to TAC trough target levels defined by the local centre standard.** TAC will be quantified at every study visit. Additional TAC quantification may be ordered by the treating physician at any time.

The TTV load will be accessed but not revealed to the investigator. TTV results must not be entered in the hospital data system used for routine care but have to be entered in the eCRF by the personnel, who performed the TTV assessment. TTV results in the eCRF will only be visible for the treating clinical personnel in the active/interventional group.

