## 6.2 REGISTRATION/RANDOMIZATION

Participants will be allocated at a ratio of 1:1 using random permuted blocks with variable block size, stratified by recruiting centre. Eligible patients will be randomized 1:1 to either

- Torque Teno virus-guided immunosuppression (arm T) or
- Standard dosing (arm S).

eCRF-based randomisation will be used. Patients will be registered at screening.

Randomization occur at visit 1 (post-transplant month 4) after confirming the inclusion/exclusion criteria. Randomization list will be created via the program nQuery-Advisor® and included in the eCRF. Implementation according to the allocation sequence will be performed by the trial personnel.

Randomization will be conducted only if the patient can be included in the study (checking of inclusion- and exclusion criteria, written consent of the patient).

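### Randomisation is stratified by centre but the interval deciding non-inferiority is not; making the planned centre-stratified interval primary is a modest, nearly free gain if event rates differ between centres

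*Protocol*

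**What the plan says.** Section 6.2 allocates patients 1:1 "using random permuted blocks with variable block size, stratified by recruiting centre". The Synopsis names 13 centres: "Berlin, Dresden, Graz, Grenoble, Groningen, Innsbruck, Leiden, Linz, Prague, Regensburg, Strasbourg, Valencia and Vienna".

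Section 10.3.3 describes the primary analysis as follows: "The difference of the occurrence of the primary endpoint between the two treatment groups and a two-sided 95% confidence interval will be calculated". No stratification factor is named. The decision rule rests on that interval: "Non-inferiority will be concluded if the upper limit of a two-sided 95% confidence interval" lies below 10 percentage points; superiority follows if the interval excludes zero. The centre-adjusted version comes next, in a supporting role: "As additional sensitivity analyses confidence intervals will be calculated being adjusted for study stratifications (such as centers) using Cochrane-Mantel-Haenszel weights". Logistic and Cox models with factors such as sex and age are also planned.

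The sample size in section 10.2 uses an unstratified two-group normal-approximation test.

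On centre practice, section 5.7.6 says of the control arm: "TAC will be dosed according to TAC trough target levels defined by the local centre standard". Section 6.17 leaves infection work-up to local standards, apart from a minimum diagnostic set, and section 6.19 does the same for treatment of rejection and infection.

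**The concern.** Blocking within centre keeps the arms nearly balanced in every centre. Differences between centres in the underlying event rate therefore largely cancel from the treatment difference. The standard error of an unadjusted difference does not credit this, because it still counts between-centre variation as noise. If centres differ, the unadjusted interval is wider than the real sampling variation and the one-sided test runs below its nominal 2.5%.

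In a non-inferiority trial the upper limit of this interval is the result. A planned analysis that follows the randomisation already exists in section 10.3.3, but as a sensitivity analysis. At stake is a small amount of power for both hypotheses.

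**Working it through.** **Inputs.** From section 10.2: event rates 0.30 (arm T) and 0.40 (arm S), margin 0.10, one-sided 2.5%, 120 per arm for the calculation and 130 per arm recruited. From the Synopsis: 13 centres. Not in the protocol, and therefore assumed: the between-centre SD of the event rate (tau), the block sizes (4 and 6) and the centre sizes.

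**1. The plan's own figure.** With unpooled variance, power = Φ(0.20 / √[(0.30×0.70 + 0.40×0.60)/n] − 1.96).
- n = 120: √(0.45/120) = 0.06124; 0.20/0.06124 = 3.266; Φ(1.306) = 90.42%. The stated figure reproduces without any centre adjustment.
- n = 130, all evaluable: 92.5%.

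**2. What stratification can remove.** In each arm, p(1−p) equals the average within-centre variance plus tau². Summed over both arms, 0.45 = within + 2·tau². An interval that credits the stratification therefore has its variance multiplied by 1 − tau²/0.225. At 120 per arm the unadjusted half-width is 1.96 × 0.06124 = 12.00 points.

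| tau | variance factor | width ratio | half-width (points) | power |
|---|---|---|---|---|
| 0 | 1 | 1 | 12.00 | 90.4% |
| 0.05 | 0.989 | 0.994 | 11.94 | 90.7% |
| 0.10 | 0.956 | 0.978 | 11.73 | 91.6% |
| 0.15 | 0.900 | 0.949 | 11.39 | 93.1% |

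**3. Simulation.** This used 13 centres, 240 patients, centre sizes either equal (18 or 19) or unequal (60 down to 4), the same risk difference in every centre, and 8,000 trials per setting. It compared an unadjusted Wald interval with the Mantel-Haenszel risk difference (Sato variance). Ranges cover the equal and unequal layouts.

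| tau | width, stratified/unadjusted | power gain (points) | type I error, unadjusted | type I error, stratified |
|---|---|---|---|---|
| 0 | 1.001–1.002 | about 0 | 2.3–2.6% | 2.4–2.8% |
| 0.05 | 0.996–0.998 | 0.3 | 2.4% | 2.5–2.6% |
| 0.10 | 0.980–0.983 | 0.5–0.6 | 2.1–2.3% | 2.4–2.6% |
| 0.15 | 0.955–0.959 | 1.1–1.5 | 1.9–2.0% | 2.5% |

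Monte Carlo error is about 0.3 points on power and 0.2 points on type I error. Type I error is taken at a true difference of +10 points (50% against 40%).

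The gain comes from a better-calibrated standard error, not from a better point estimate. With equal centres and tau 0.15, both estimates had an empirical SD of 5.89 points. The unadjusted interval implied 11.96/1.96 = 6.10 points, and the stratified interval 11.43/1.96 = 5.83.

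**4. Second simulation at full size.** With 260 patients, unequal centres and 6,000 trials per setting, tau 0.10 moved the half-width from 11.5 to 11.3 points and power from 93.1% to 93.8%. Tau 0.15 moved them from 11.5 to 11.0 points and from 92.5% to 93.8%. Type I error was 2.3–3.1% for the unadjusted interval and 2.4–3.0% for the stratified one.

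**5. Where power is lower.** Section 10.2 regards arm T rates of 20 to 30% as reasonable. For superiority at 25% against 40% with 130 per arm, √[(0.1875 + 0.24)/130] = 0.05735 and 0.15/0.05735 = 2.616, so power is Φ(0.656) = 74.4%. Applying mid-range width ratios from step 3 as an approximation, 0.982 gives 75.9% and 0.957 gives 78.0%.

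**The case against.** The strongest reply is that nothing in the plan is wrong. The sample size and the primary analysis are both unstratified and agree with each other. The stated power is right, the unadjusted interval errs on the cautious side, and the centre-adjusted interval is already pre-specified. All of this stands.

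The protocol also limits centre variation in how endpoints are ascertained. Section 3.2 has infections and biopsies re-assessed by two blinded assessors who must agree, and section 6.17 sets a minimum diagnostic work-up. This stands in part. Central assessment makes classification more uniform, but it does not remove differences in control-arm dosing, or in whether an infection leads to day-care, drug treatment or reduced immunosuppression. Those responses form part of the endpoint definition.

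Three stronger readings are tempting, and the protocol supports none of them:
- A reader might infer that the deciding interval is certainly too wide. That holds only if centres differ, and the protocol does not say by how much. Without such differences the stratified interval is very slightly the wider one.
- A reader might infer that the trial is underpowered or its non-inferiority claim unsafe. The 90.42% reproduces, and the simulations show no systematic inflation of type I error from the unadjusted interval.
- A reader might infer that no planned adjusted analysis can be read against the margin. The Mantel-Haenszel interval can. Only the logistic and Cox models, as described, yield odds and hazard ratios that cannot be set directly against 10 percentage points.

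The protocol also never calls the primary interval unadjusted. That follows from adjustment being introduced as an additional analysis, which is the natural reading but still an inference.

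**Conclusion.** The point holds as a matter of efficiency and of matching the analysis to the design. The primary analysis does not use the factor on which randomisation is stratified, and the analysis that does is ranked second. At an assumed between-centre SD of 10 points, the change narrows the interval by about 2% and adds about half a point of power in the planning scenario. At 15 points it narrows it by 4 to 5% and adds about 1 to 1.5 points. With no centre differences, the loss is about 0.2% of the width. These figures assume a constant risk difference across centres, blocks of 4 and 6, and illustrative centre sizes. The between-centre SD drives the result and cannot be taken from the protocol. No claim in the plan becomes false if the sponsor keeps the unadjusted interval, but the choice should then be justified.

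**What to change.** In section 10.3.3, name as the primary analysis the Mantel-Haenszel risk difference stratified by recruiting centre, with its two-sided 95% confidence interval, and use it for both the non-inferiority and the superiority decision. State a rule for pooling very small centres, fixed before unblinding. The average is only 260/13 = 20 patients per centre, and a centre with patients in one arm only contributes nothing to the stratified estimate. Keep the unadjusted difference as the sensitivity analysis.

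Optionally, also report the adjusted logistic model as a standardised risk difference, so that it can be read against the 10-point margin.

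The cost is an exchange of roles between two analyses already in section 10.3.3, plus the pooling rule and, if adopted, the standardisation method. It needs no new data and no change in sample size. It should be settled before outcomes are seen by arm, because choosing between the two intervals afterwards would not be credible.
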